## Abstract

**Background:**

Co-bedding, a developmental care strategy, is the practice of caring for diaper clad twins in one incubator (versus separating and caring for each infant in separate incubators), thus creating the opportunity for skin-to-skin contact and touch between the twins. In studies of mothers and their infants, maternal skin-to-skin contact has been shown to decrease procedural pain response according to both behavioral and physiological indicators in very preterm neonates. It is uncertain if this comfort is derived solely from maternal presence or from stabilization of regulatory processes from direct skin contact. The intent of this study is to compare the comfort effect of co-bedding (between twin infants who are co-bedding and those who are not) on infant pain response and physiologic stability during a tissue breaking procedure (heelstick).

**Methods/Design:**

Medically stable preterm twin infants admitted to the Neonatal Intensive Care Unit will be randomly assigned to a co-bedding group or a standard care group. Pain response will be measured by physiological and videotaped facial reaction using the Premature Infant Pain Profile scale (PIPP). Recovery from the tissue breaking procedure will be determined by the length of time for heart rate and oxygen saturation to return to baseline. Sixty four sets of twins (n = 128) will be recruited into the study. Analysis and inference will be based on the intention-to-treat principle.

**Discussion:**

If twin contact while co-bedding is determined to have a comforting effect for painful procedures, then changes in current neonatal care practices to include co-bedding may be an inexpensive, non invasive method to help maintain physiologic stability and decrease the long term psychological impact of procedural pain in this high risk population. Knowledge obtained from this study will also add to existing theoretical models with respect to the exact mechanism of comfort through touch.

**Trial registration:**

NCT00917631

## Background

An increasing number of multiple pregnancies and increasing obstetric intervention at preterm gestation has led to a rising number of preterm twin infants being admitted into Neonatal Intensive Care Units (NICU). These preterm infants undergo repeated and often untreated procedural pain that can contribute to immediate stress and may have a long term impact on the normal maturation of regulatory systems. The practice of co-bedding twins simulates various aspects of the intrauterine environment. Co-bedding allows twins to remain in close proximity and have skin-to-skin contact with each other, thus creating opportunity for familiar recognition of auditory and olfactory stimuli and for a continuation of the twin relationship that began in utero.

Given the potential benefits of co-bedding, theoretical and conceptual underpinnings, and compelling evidence related to the effects of environmental context, it is important to examine the possibility that twins placed in close proximity could provide comfort and protection against the numerous stressful procedural assaults experienced during hospitalization. The intent of this study is to compare the comfort effect of co-bedding (contrasting twin infants who are co-bedding versus those who are not) on pain response during a tissue breaking procedure (heelstick). Pain response will be measured in all infants and will be determined by physiological and behavioral reaction.

## Summary of Literature Review

### a. Recent increase in twin births and preterm births among twins

During the past two decades, significant advances in medical technology have contributed to the increased survival of critically ill, preterm, and very low birth weight infants [1]. As mortality rates have declined, the focus has shifted to decreasing morbidity and adverse neurodevelopmental outcomes for these high-risk infants [2]. An additional change in the surviving population within NICU's is that the numbers of twins admitted has escalated as the occurrence of multiple births is continuing to rise in North America [3]. In Canada, multiple births increased from 2.1 per 100 total births in 1991 to 2.7 per 100 total births in 2000, [4] and to 3.0 per 100 total births in 2004 [5]. Advanced maternal age and increased fertility treatments have been reported as the main reasons for this increase [3,6-8]. These factors have been primarily associated with a rise in dizygotic twins. Although race has some effect on the on the incidence of dizygotic twinning (10-40 per 1000 live births among people of African descent compared to 7-10 per 1000 among people of European descent), higher maternal age and assisted reproductive technologies are strongly associated with multiple gestation [9]. Occurrence of monozygotic twinning has been less affected with a stable incidence of 4 per 1000 total births worldwide.

Preterm birth is the leading cause for hospitalization during the neonatal period and is responsible for more than 75% of all cases of perinatal morbidity and mortality [10]. The incidence of preterm birth among multiples has risen substantially over the past several decades in North America. In the United States, preterm birth rates among twins increased by 19.6%, from 40.9% in 1981 to 55% in 1997 [11] and to 60.5% in 2005 [12]. In Canada, the rate of preterm birth among twin live births increased by 14.5%, from 42.5% between 1985 and 1987 to 49.6% between 1994 and 1996 [13], to 53.0% in 2000 [4] and 57% in 2004 [14]. Furthermore, twin pregnancies that followed assisted reproduction were more likely to result in lower mean gestational age (33.1 versus 34.2 weeks) and mean birth weight (2,029 versus 2,177 g for the first twin and 1,897 versus 2,136 g for the second twin) than those occurring spontaneously, with longer associated NICU stays [15]. In a similar study in 2002, examining the effect of multiple births on perinatal indicators over two decades in Canada, the British Isles, France and the Unites States, twins contributed to a disproportionate share of preterm deliveries and low birth weight newborns [16]. Maternal and neonatal complications associated with twin pregnancies also contribute to the increased likelihood of NICU admission and prolonged hospitalization. Excess maternal risks in twin pregnancies include gestational hypertension, placental abruption, and placenta previa, all which are positively correlated with adverse neonatal sequellae [17]. In a 2005 Canadian review of 3,242 infants born at or before 32 weeks of gestational age and admitted to 24 Canadian NICUs, twins had approximately similar mortality when gestational age and severity of illness were accounted for (adjusted odds ratio 1.3, 95% confidence interval 1.0-1.6) [18]. Weight discordance, chorionicity, and gestational age at birth were more closely associated with adverse outcomes than plurality of pregnancy [19]. However, the higher likelihood of these factors in twin versus singleton birth created the additional morbidity risk associated with multiple births [20].

### b. Ubiguitous pain exposure in the neonatal intensive care unit

Given the higher likelihood of preterm birth and associated morbidity leading to the need for NICU admission, twin infants often face increased medical challenges and can be neurodevelopmentally less prepared to cope with multiple stimuli after birth when compared to healthy full-term infants [21]. Data from several countries have consistently shown that neonates undergo multiple painful and stressful procedures during hospitalization in the NICU. Scandinavian [22] and British [23] studies report an average of 10-15 procedures daily with younger neonates (< 28 weeks) undergoing as many 700 painful procedures during their hospital stay [24]. Recently, Carbajal [25] conducted a 2-week prospective chart review of 431 infants in 13 European NICUs. These infants endured 60, 969 painful procedures and a mean of 16 exposures (range 0 to 62) of painful or stressful procedures per day. Pain management for infants undergoing procedural pain associated with most frequent procedures such as tracheal suctioning, heelstick, tape removal, venepuncture and intravenous line insertions, although improved in recent years, was suboptimal. Almost 40% of infants undergoing heelstick for blood collections, the most commonly performed tissue breaking procedure in the NICU setting, did not receive any form of non-pharmacologic or pharmacologic intervention and 41% of infants underwent tracheal intubation without the benefit of any pain relieving strategies [25]. In a similar 1-week prospective chart review of pain practices in 14 tertiary level NICU's in Canada, Johnston and colleagues [26] reported that 582 infants underwent a total of 30,416 procedures. Thirty-five different procedures were identified with 3553 (11.7%) being classified as tissue breaking (i.e. skin-breaking or endotracheal intubation or an ophthalmologic examination). On average infants had 26 exposures (0-469) per week, just less that 4 per day. Although these findings support a slight reduction in previously reported average number of daily painful procedures that infants in the NICU endure, pain relieving strategies were still not routinely used. Forty-six percent (tissue) and 57% (non-tissue) damaging procedures performed were not accompanied by any form of pain relieving treatment.

Animal studies have linked pain to adverse developmental changes in the brain [24,27] and in the spinal dorsal horn [28,29]. In human infants, immediate responses to untreated pain such as physiological elevations in heart rate, blood pressure, and oxygen requirements, can lead to fluctuations in intracranial pressure, possibly leading to intraventricular hemorrhage (IVH) and periventricular leukomalacia [30,31]. Increased stress hormone release triggered by pain impedes normal regulation of growth and tissue repair [32] and has adverse effects on cognition, memory, and behaviour systems [33]. Stress associated with pain can lead to prolonged structural and functional alteration in pain pathways that lasts into adult life, permanently altering normal or common responses to pain [34,35]. Given the extreme plasticity of the preterm brain and immature regulatory processes, it is not surprising that exposure to repeated skin breaking procedural pain may disrupt the normal development of physiological, hormonal, behavioural and hypothalamic-pituitary-adrenal (HPA) axis that may contribute to these long term effects. Recently, Grunau and colleagues have reported a blunting of hypothalamic-pituitary-adrenal (HPA) axis response in infants who had undergone numerous painful procedures in the NICU [29,36]. Preterm infants in contrast to infants born at term [37,38] appear to experience a down-regulation of behavioural responses and a decrease in sympathetic recovery contributing to higher physiological instability.

Despite a surge in the literature illustrating various methods to accurately assess and manage pain and the provision of consensus practice guidelines [39] minimal improvement in the treatment of pain associated with routine NICU procedures has ensued. The reasons for this lack of practice change are unclear. Issues related to research utilization (i.e. education, unit context and institutional facilitation) and lack of consensus regarding optimal pain management strategies for routine procedural pain are the most likely cause. In addition, evidence that morphine (a commonly used neonatal analgesic) which is known to attenuate postoperative and severe pain, is less effective for pain associated with mechanical ventilation and heelstick [40] as well as possible adverse outcomes associated with its prolonged use [41] has led to further inquiry regarding the role of non-pharmacologic measures and environmental context in the minimization of acute pain.

### c. Environmental context and comfort for alleviation of pain

Infants have been shown to have cortical perception [42,43] and memory of pain, both exhibited by peripheral hypersensitization [37] and behavioural response [29,44,45]. Recently, two studies using near infrared spectroscopy (NIRS) to measure pain experience in preterm infants, revealed that infants as young as 28 weeks of gestation exhibit cortical response during heelstick [42,43]. Functional MRI imaging of adults has demonstrated that pain perception and inhibitory mediation appears to involve multiple areas of the brain, referred to as the "pain matrix" [46], and that perception and response can be mediated by visual cues and relational factors [47]. Although not yet proven with neonatal neuroimaging, the assumption that neonates may also perceive and respond to pain and distress in a similar interlinked manner is highly plausible. It is known that pain in newborns can be soothed with alterations in environmental context and provision of non-pharmacological interventions involving orogustatory, vestibulokinesthetic, and/or olfactory and tactile systems. Sweet tasting solutions, breastfeeding and nonnutritive sucking regulated through endogenous opiate and serotonin systems have been shown to diminish pain response associated with procedural pain [48-51]. Containment, felt to enhance regulation of infant state via swaddling and facilitated tucking have also been shown to be beneficial [49]. Although the benefits of music and vestibular action may be less promising in isolation (i.e., without the mother), these results have helped us better understand the importance of maternal presence and relationship with respect to pain response [52,53].

Both term and preterm infants have olfactory memory. They not only show preference for their own mother's amniotic fluid and breastmilk, but this recognition has been shown to diminish crying during maternal separation and pain response during heelstick [54-57]. Interestingly, olfactory recognition of a familiarized smell can illicit a similar comforting response [58,59] indicating both memory and ability to learn, remember and have emotional connections even in young, very preterm infants. Kangaroo mother care (KMC) or skin-to-skin care (SSC) provides a multisensorial context encompassing tactile, olfactory, and relational systems. It has been shown to diminish pain response and improve physiological stability in both term and preterm infants [60-66]. Whether the mother is an essential aspect of this comfort during skin-to-skin contact has yet to be proven.

The discovery and practice of new and innovative approaches to minimize the effects of infant pain should be a primary focus of neonatal health care researchers [67]. Numerous possible non-pharmacologic measures or alternative environmental contexts within the NICU have yet to be fully explored as primary or adjunctive methods to relieve pain and diminish potential long lasting effects of pain on the development of regulatory pathways. The increased incidence of multiple gestation births and admission of these fragile babies to neonatal units also raises questions regarding the differences in care of twins and higher order multiples versus singletons. Despite the ever increasing numbers of at-risk twin infants, specific interventions targeted at this population have not been studied.

### d. Co-bedding as a potential comfort measure

At birth, preterm twins are typically separated as individual health needs are met. This leads to an interruption in their shared uterine environment and disrupts the expected developmental trajectory of a twin pregnancy. Co-bedding of twins is an example of a developmental care initiative. Its purpose is to minimize neurodevelopmental sequellae associated with admission to a NICU [21,68,69]. The practice of co-bedding is based on the premise that extrauterine adaptation of preterm twins is enhanced by continued physical contact with the other twin rather than sudden deprivation of such stimuli [69,70]. Maintaining this presence may assist twins to cope with pain associated with routine procedural pain by stabilizing self regulatory pathways.

In summary, twins, the majority of whom are born preterm, are exposed to painful procedures as part of their essential medical care. The adverse effects are both immediate and potentially long-term, affecting future sensation and behaviour [27,34,71]. Given that the practice of co-bedding simulates numerous aspects of environmental context - proximity, tactile, olfactory, auditory, memory and relationship - that have been shown to provide comfort to newborns, it is reasonable to propose that the contact or presence of a twin who has shared the same uterine space since conception would have a similar comforting effect.

## Purpose

The purpose of this study is to determine the efficacy of twin comfort during a tissue breaking procedure (heelstick) in the NICU.

## Hypotheses

The pain response of a twin undergoing a heelstick will be significantly altered when co-bedding.

## Methods/Design

### a. Study Objectives

The intent of this study is to evaluate the effect of co-bedding among at-risk twins on pain response during a painful procedure. Secondary objectives include the effect of twin co-bedding on changes in physiologic stability and recovery following the painful procedure, heart rate variability, salivary cortisol, frequency of dosages of 24% sucrose given during painful procedures and the response of the twin not receiving the tissue breaking procedure.

### b. Study design

We propose to carry out a randomized controlled trial comparing the comforting effect of co-bedding on twins undergoing a tissue breaking procedure in the NICU.

### c. Study population

The source population consists of all twin pairs admitted to a tertiary level NICU at the IWK Health Centre, Halifax, Nova Scotia and St. Justine Hospital, Montreal, Quebec, who are considered medically stable and who require at least one medically indicated heelstick for blood procurement.

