## What are the proposed methods of protecting against sources of bias?

Due to the unblinded nature of the intervention, it is important to strictly adhere to rigorous methods to eliminate potential bias. The use of an off-site computerized website for group allocation will decrease the risk of allocation bias. The individuals coding pain response will be blinded to the twins treatment status (whether co-bedding or receiving standard care). The video camera will be set up to focus only on the infant's face and will be controlled by the investigator or research nurse. Coding of pain scores will be calculated using the Premature Infant Pain Profile (PIPP) [72]. The PIPP is considered a reliable and valid tool to measure procedural pain in both preterm and term neonates [73-75]. Both composite PIPP scores and combined behavioral (facial) indicators will be reported in each group. Coding will be carried out at McGill University at [name] lab by 2 coders (coder A and coder B). Each coder will only code data on infants who are co-bedding (A) or code data on infants who are receiving standard care (B). Coders will not enter the unit, communicate with each other or compare data sets (i.e. PIPP scores will be estimated without knowledge of group assignment). The use of different coders (who have no previous knowledge of patient enrolment and randomization to code separately for infant facial responses, etc and who will remain blinded to each other's assessments), is expected to minimize observer bias. Research coders A and B will be trained separately by the principal investigator and a member of [name] research lab team. Training will be standarized and coding performances assessed so that an interclass coeffecient (ICC) of 0.85 is reached between the coders' standarized scores. Following the initial training, coders will be retested quarterly using standarized videotapes to ensure inter-rater reliability. If the ICC drops below 0.75, re-training and re-coding will take place. This reliability check conducted with standarized tools will minimize the likelihood of observer bias. Every three months, coders A & B will also re-code two randomly selected videotapes from the first weeks of coding to ensure intra-rater reliability. ICC's of 0.75 will be considered the cutoff point of acceptability. Following study completion, previously assigned group coders will be asked to code a random selection of approximately 20% (n = 6) of the tapes from the alternate group. Inter-rater scores will be correlated to ensure that if differences are found between the groups, these differences are related to the intervention of co-bedding and not to systematic error between the two coders scoring techniques.

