## What is the proposed frequency and duration of follow-up?

Data will be collected simultaneously on both the infant undergoing the heelstick and his/her twin. Data collection using monitoring (Somté and Massimo oxygen saturation systems) and video-tape recording will take approximately 20 minutes per participant - a baseline period (1-2 minutes prior to heelstick), warming (2-3 minutes), heelstick (2-5 minutes), and recovery phase (approximately 1-10 minutes).

If both infants require a medically indicated heelstick on the same day, they will occur no less than 30 minutes apart.

All chart data will be collected following randomization and data collection will continue until completion of the heelstick. Prior painful procedures will include all procedures from birth until completion of heelstick.

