We based our PIPP score assumptions on previous studies which reported PIPP scores of 10.7 (2.3) vs. 12.9 (2.5) from a study on kangaroo skin-to skin care versus incubator care in preterm infants 32-36 weeks of gestational age [61] and PIPP scores 8.9 (*CI *7.9-9.9) versus 10.7 (*CI *9.6-11.8) in preterm infant 28-31 6/7 weeks of gestational age. Based on these reported 0.5 and 0.6 standard deviation pain scores [66] and the reported values in the above studies, we used a conservative standard deviation estimate of 2.0 as our proposed study population will encompass both groups of infants. Sample size was calculated using a 2-sided alpha error of 0.05 and a power of 80 percent. We designed the study to detect a difference of 1 point or greater change (SD 2.0) in the PIPP scores. One hundred and twenty-eight infants would be required to identify this variation in the PIPP scores if such a difference is in fact caused by co-bedding. With this sample size, we will also have over 95% power to detect a greater than 15 second mean difference in physiological recovery (heart rate and oxygen saturation) between groups. In a recent study of skin-to-skin care [66], the time to return to baseline heart rate following the application of the plaster signifying the end of the procedure was significantly different, 123 seconds (*CI *103-142) for the Kangaroo Mother Care condition and 193 seconds for Incubator condition (*CI *158-227, *p *< .00001). Since all infants will receive 24% sucrose, we do not expect that the differences seen in time to recovery will be this large. Therefore, by using the larger sample, and conservatively accounting for the use of regression techniques, our study will recruit 128 participants (64 sets of twins, 32 assigned to the co-bedding group and 32 to the standard group).

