## Will compliance be a concern?

We have conducted a previous pilot study [76] and are conducting a larger clinical trial examining twin regulation during co-bedding over an extended period of time and have not encountered issues related to compliance. Given the short duration of data collection (during one heelstick procedure), we do not anticipate problems with compliance. Nevertheless, we will monitor compliance to group allocation through daily observation and direct staff communication.

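### The 80% power is a best case: it needs a study heelstick in every one of the 128 infants and independent outcomes within pairs, and the protocol secures neither

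*Protocol article*

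**What the plan says.** **Sample Size.** The inputs are a 1-point PIPP difference, SD 2.0, and "a 2-sided alpha error of 0.05 and a power of 80 percent". The result is given in infants: "One hundred and twenty-eight infants would be required to identify this variation in the PIPP scores". Recruitment is then set at the same 128, as 64 pairs with 32 per arm.

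**Who supplies the primary outcome.** The analysis section defines it as the pain response of the infant who has the tissue-breaking procedure. The response of the twin who is not having the procedure is a secondary outcome. The follow-up section describes the recording: "Data will be collected simultaneously on both the infant undergoing the heelstick and his/her twin".

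**How many heelsticks a pair will have.** Section c (Study population) takes twin pairs "who require at least one medically indicated heelstick for blood procurement". The study heelstick must fall within 10 days (sections on co-bedding care and standard care). The Ethics section says heelsticks are usual care and are not done for the study alone.

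**Coding check.** After the study each coder re-codes "approximately 20% (n = 6) of the tapes from the alternate group".

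**Text pointing to both twins.** The Background says pain response is measured in all infants. The standard care section has the twins undergo a heelstick. The analysis section plans GEE to correct for dependence within pairs.

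**The concern.** The sample size calculation fixes the number of primary outcomes at 128. The eligibility wording, read on its own grammatical subject (the pair), promises one heelstick per pair. An infant with no medically indicated heelstick in the window has no primary PIPP score, and none can be added for research purposes. The number of primary outcomes therefore depends on how many pairs supply two heelsticks, and the article gives no figure for that.

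The power claim uses the maximum possible count and treats twins as independent, although the analysis plan expects dependence. If fewer infants contribute, a null result would be weaker evidence against a 1-point effect than the stated 80% suggests. The protocol itself calls 1 point clinically significant.

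**Working it through.** **Inputs from the Sample Size section:** difference 1, SD 2.0 (standardised difference 0.5), two-sided alpha 0.05, 32 pairs per arm.

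**Inputs not in the document (assumed, with ranges):** the share q of pairs in which both twins have a study heelstick, from 0 to 1; the within-pair correlation ICC, 0 and 0.3 in the table and 0.5 as a further case.

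**1. Reproduce the stated figure.** The normal approximation gives 2 × (1.960 + 0.842)² × 2.0² / 1² = 62.8, so 63 per arm and 126 in all. The t-test version gives 64 per arm (power 0.801), so 128 in all. The stated number is reproduced exactly, and only with 64 independent outcomes per arm. The recruited number is also 128, so the remark about conservatively allowing for regression adds no infants.

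**2. Effective sample size per arm.** A pair with one outcome carries one unit of information. A pair with two carries 2/(1 + ICC). Hence

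n_eff = 32 × [(1 − q) + 2q/(1 + ICC)].

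Examples:
- ICC 0, q = 0.5: 32 × (0.5 + 1) = 48.
- ICC 0.3, q = 0.5: 32 × (0.5 + 1/1.3) = 40.6.
- ICC 0.3, q = 1: 32 × 2/1.3 = 49.2.

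**3. Power for 1 point, and difference detectable with 80% power (two-sample t-test).**

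| Share of pairs with two outcomes | Outcomes in total | ICC 0: n_eff per arm | Power | Detectable | ICC 0.3: n_eff per arm | Power | Detectable |
|---|---|---|---|---|---|---|---|
| all (q = 1) | 128 | 64 | 0.80 | 1.00 | 49.2 | 0.69 | 1.14 |
| half (q = 0.5) | 96 | 48 | 0.68 | 1.16 | 40.6 | 0.60 | 1.26 |
| none (q = 0) | 64 | 32 | 0.50 | 1.42 | 32 | 0.50 | 1.42 |

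The table assumes at least one outcome from every pair. At ICC 0.5 with q = 1, n_eff is 32 × 2/1.5 = 42.7 and power is 0.63.

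**4. Tape count.** 6/0.20 = 30 tapes in a group. Twenty percent of 32 is 6.4 and of 64 is 12.8. The stated 6 therefore fits about one tape per pair, whereas the sample size needs 64 heelstick tapes per arm.

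**The case against.** The strongest reply is that both twins are meant to be tested. The Background speaks of all infants, and the standard care section has the twins undergo a heelstick. The co-bedding section sets a minimum co-bedding time before heelstick for all infants, and the Sample Size section expects all twins to receive sucrose before heelstick. A GEE correction for pairing in the paragraph on the primary comparison would be unnecessary with one outcome per pair. The relative clause in section c could also be read infant by infant, as its companion clause on medical stability is in section d. A twin described as not having the procedure may simply be filling that role on one occasion and be tested on another. The tape count is indirect and could be a slip.

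Most of this stands. It shows that both twins are expected to contribute, at least in many pairs. A reader might therefore go too far in three ways:

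- **Taking the trial to have about 50% power.** The documents do not support this. That figure needs every pair to give exactly one outcome, which the GEE plan and the passages above speak against.
- **Taking the sentence about both infants needing a heelstick as proof that second heelsticks are rare.** It is a spacing rule for heelsticks on the same day and says nothing about their frequency.
- **Taking 64 outcomes as a guaranteed minimum.** A pair could pass through the 10-day window with no heelstick in either twin.

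What the reply does not supply is any passage that requires a heelstick in each twin or states how many pairs will give two. It also leaves the tape count unexplained. The full protocol may give an expected number of heelsticks per pair, but the power claim and the wording it conflicts with both stand in this article.

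**Conclusion.** The arithmetic behind 128 is right. The 80% it supports is the top of a range, reached only if every infant has a study heelstick within 10 days and outcomes within a pair are uncorrelated. If every pair gives at least one outcome, power for 1 point runs from 0.80 down to about 0.50, and the detectable difference rises from 1.00 to 1.42 points. If half the pairs give two outcomes, power is about 0.68 with ICC 0 and 0.60 with ICC 0.3.

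The two causes should be kept apart. At ICC 0.3, power is already 0.69 with every twin tested, so going from all pairs to half of them giving two outcomes costs a further 0.09 or so. At ICC 0 the same step costs about 0.12.

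The share of pairs and the ICC are assumptions, since the article gives neither. The firm conclusion is that the article is inconsistent about how many primary outcomes it will have, and that its single power figure uses the most favourable case.

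**What to change.** 1. In Sample Size, state whether each twin is expected to contribute a heelstick PIPP score, and bring section c into line with that statement.
2. State that every twin with a medically indicated study heelstick in the window enters the pair-clustered GEE under its randomised arm.
3. Report, by arm, the randomised infants who have no study heelstick. The primary set is defined by an event after randomisation in an unblinded trial, so it must be reconciled with the stated intention-to-treat principle.
4. Replace the single 80% claim with power and detectable difference over a stated range for the share of pairs giving two outcomes and for the within-pair correlation, as in the table above. Do not state that at least 64 outcomes are guaranteed.
5. Put the 20% re-coding sample on the same base: about 13 tapes if there are 64 per arm, 6 if there are about 32.

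The cost is some wording, one recalculation, a less favourable stated power and, if 64 tapes per arm is the right base, about seven more tapes for each coder to re-code. No extra infants or heelsticks are needed.
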